### Study blinding

2.6

Only the researcher responsible for conducting the treatments (who will open the randomized envelopes) will know which treatment is assigned to each patient. The identification of each group will only be revealed by this researcher after statistical analysis of the data for all those involved in the study. Therefore, the researcher responsible for data collection, the microbiologist and the statistician will be blind regarding the treatments assigned to the groups. The patient will also be blind to the type of treatment performed, since the periodontal treatment will be identical in both groups and treatment with PDT will be simulated in the control group.

### Pretreatment evaluations

2.7

Participants will sign the ICF, TA (when necessary), the anamnesis, periodontal clinical examination and the OHIP-14 questionnaire will be done. These data will be collected by 1 calibrated researcher. Collection of saliva and biofilm from all patients will be performed to evaluate the inflammatory cytokines (according to item ‘Salivary and biofilm cytokines profile’) and for microbiological evaluation (according to the item “Microbiological analysis”). Following which, OHG will be given to all patients, and then the treatment in accordance with the randomization.

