### Methodology used for the clinical evaluation of gingivitis

2.9

It will be performed by an evaluator calibrated with periodontal probe in millimeters (Periodontal probe from the University of North Carolina UNC-15 - Hu-Friedy^TM^). The periodontal probe will be inserted at all predetermined sites at the gingival margin of all teeth, 30 seconds will be waited and, at the smallest sign of bleeding, the presence or absence of bleeding will be noted, in a dichotomous manner, for that site.^[34]^ Gingival bleeding will be evaluated at 6 sites (mesiobuccal, buccal, distobuccal, mesiolingual, lingual, distolingual).

Gingival index:

Presence (1) of bleeding with probing at gingival margin,^[34]^ or

Absence (0) of bleeding with probing at gingival margin.^[34]^

The gingival Index will be presented in a percentage (%). The result will be based on the ratio of total sites to sites affected (with bleeding)^[34]^

Results will be considered indicative of gingivitis with ≥ 10% bleeding.^[13]^

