#### Clinical probing depth

2.14.1

It will be performed by a calibrated evaluator using a periodontal probe marked in millimeters (North Carolina University periodontal probe, UNC-15 (Hu-Friedy^TM^): all teeth (except third molars) will be evaluated at 6 sites (mesiobuccal, buccal, distobuccal, mesiolingual, lingual, distolingual) using the aforementioned parameters.

The North Carolina University periodontal probe will be insert in the gingival sulcus. Probing depths to be evaluated in millimeters (mm) from the base of the periodontal pocket to the free gingival margin.

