#### Gingival index

2.14.3

It will be evaluated by recording the presence or absence of bleending up to 30 seconds after the determination of probing depht. The number of positive sites bleeding will be record and than expressed as percentage of the number of sites examined. Using the following score of bleeding when probing gingival margin: Presence = 1; Absence = 0

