##### Biofilm collection

2.14.5.1

Biofilm samples from regions with gingivitis and gingival hyperplasia (pseudo pocket) will be collected from the supragingival portion to avoid contamination of the sample. The site is isolated with cotton rolls. The paper cone is inserted until resistance is felt. The cone will remain in this position for 30 seconds. If there is blood contamination a new cone will be used after 90 seconds. Five cones must be collected, one for each cytokine. The cones will be placed in a 1.5 ml microcentrifuge tube (Eppendorf) and stored at -80°C. During collection they will be properly identified and stored on ice inside a Styrofoam container. The collected samples will be stored at -80°C until further analysis is performed.

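### Saliva and crevicular samples are listed after the bleeding-provoking periodontal examination, no visit requires sampling before probing, and saliva has no blood check

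*Protocol article*

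**What the plan says.** All references are to the protocol article.

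- **Section 2.7 (Pretreatment evaluations).** After consent, "the anamnesis, periodontal clinical examination and the OHIP-14 questionnaire will be done". The sampling sentence comes next: "Collection of saliva and biofilm from all patients will be performed to evaluate the inflammatory cytokines", and for microbiology. The section closes with "Following which, OHG will be given to all patients, and then the treatment in accordance with the randomization".
- **Section 2.14.1 (Clinical probing depth).** The examination is full-mouth: "all teeth (except third molars) will be evaluated at 6 sites".
- **Section 2.14.3 (Gingival index).** Bleeding is read from that probing, as "presence or absence of bleending up to 30 seconds after the determination of probing depht".
- **Section 2.9 (clinical evaluation of gingivitis).** Participants are identified by bleeding: "Results will be considered indicative of gingivitis with ≥ 10% bleeding".
- **Section 2.14.5.1 (Biofilm collection).** Two precautions apply to the paper cones: "The site is isolated with cotton rolls", and "If there is blood contamination a new cone will be used after 90 seconds".
- **Section 2.14.5.2 (Saliva collection).** It gives the volume, the tube and the storage of unstimulated saliva. It has no check for blood, no discard rule and no timing relative to probing.
- **Section 2.13 (Study variables).** GI is the primary variable. Five cytokines and the 16S rRNA bacterial count are secondary variables, each measured in saliva and in crevicular fluid at T0, T1 and T2.

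**The concern.** The examination is meant to provoke bleeding, and the protocol itself treats blood as a contaminant of the cones. If saliva is collected after the probe has been round the whole mouth, it can contain blood that the examination released.

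That contamination would probably not be constant. It would tend to be greater where more sites bleed, that is, where GI is higher. If GI falls from T0 to later visits, or falls further in one arm, the amount of blood in saliva could fall with it. A change or difference in salivary cytokines could then partly reflect bleeding on probing and not a separate change in local cytokine production. The Discussion presents clinical, microbiological and biomarker analysis as three lines of evidence. Their agreement counts for less if one of them partly inherits the bleeding score.

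**Working it through.** The plan states no figure on this point, so there is none to reproduce. The check sets the sections side by side and adds one count for scale.

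**1. Order at T0.** Section 2.7 lists examination, then sampling, then guidance and treatment. Its only explicit order words place guidance and treatment after sampling; no such word joins examination to sampling. Probe-then-sample is therefore a reading of the listing. Two things support it. Eligibility needs a bleeding percentage and a probing depth (sections 2.2 and 2.9), and the cones come from pseudopocket sites (section 2.14.5.1), which the protocol describes through probing depth. No section puts sampling first.

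**2. Order at T1 and T2.** Section 2.7 covers the pretreatment visit only. The text gives no order of sampling and probing for days 7 and 21.

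**3. Does the protocol fix order elsewhere?** Yes. Section 2.14.2 has plaque scored before probing depth. No equivalent rule exists for the samples.

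**4. Safeguards against blood.**

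| Sample | Isolation | Rule if blood is seen | If blood persists |
|---|---|---|---|
| Paper cones | Cotton rolls | New cone after 90 seconds | Not stated |
| Saliva | Not applicable | None | None |

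**5. Scale of the probing.** The number of teeth is an assumption, because the document does not give it. Sites probed = teeth × 6. Minimum bleeding sites at entry = 10% of sites, rounded up.

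- 28 teeth: 28 × 6 = 168 sites; 0.10 × 168 = 16.8, so at least 17 bleed.
- 24 teeth: 24 × 6 = 144 sites; 0.10 × 144 = 14.4, so at least 15 bleed.

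These counts show that bleeding before sampling would be routine at T0 under the listed order. They do not measure blood volume, since GI scores each site only as bleeding or not.

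**6. From bleeding to bias.** The document gives no blood volume, no cytokine level in blood compared with saliva or crevicular fluid, and no link between blood and 16S copies. Neither the size of any effect nor its direction for a given marker can be derived.

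**The case against.** **The order is inferred.** A reader might take section 2.7 to say that samples are taken after probing. It does not say so in words; its opening can be read as an inventory, and where the protocol wants an order, as for plaque, it states one. The flowchart and the SPIRIT figure are not shown and might settle the matter. This stands as a limit on the wording. It does not remove the point: the order in print is the unfavourable one, and nothing in the text shown prevents it.

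**An article may leave visit procedures to the full protocol.** This is fair for missing detail in general. Here, however, the article does list a sequence, and it goes down to cone dwell time and the 90-second wait.

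**Crevicular samples are protected.** Largely so. It would be wrong to treat cones like saliva. What remains is that a second bloody cone has no rule.

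**Both arms are examined alike by a blinded examiner.** This is correct, and the primary variable is untouched. The order creates no difference between arms by itself. If the arms do differ in bleeding, though, equal procedures would not stop that difference from passing into saliva.

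**A halving of blood might be inferred.** With 28 teeth, a fall in GI from 10% to an assumed 5% takes bleeding sites from about 17 to about 8 (0.05 × 168 = 8.4). A reader might conclude that blood in the samples halves. The document does not support this: a count of positive sites is not a volume, and a whole-mouth count says little about cones from the four pre-determined sites named in the Abstract.

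**The bacterial count.** A reader might extend the argument to the 16S result. Probing a pocket before sampling could plausibly disturb its contents, but nothing in the document ties blood to 16S copies. This part is weak.

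**Conclusion.** The point holds as a cheap improvement to how secondary biomarkers are collected. Section 2.7 lists sampling after the periodontal examination, no section requires samples before probing at any visit, and saliva has no blood check. Read in that order, probing-provoked blood can enter the samples, chiefly saliva.

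The further consequence, that salivary cytokine differences could partly follow GI, rests on two assumptions: that the listed order is what sites will do at T0, and that it is repeated at days 7 and 21, where the text is silent. Its size is unknown. The documents do not support saying that the samples do carry blood, that the cytokine or bacterial results restate the bleeding index, or that the comparison of GI between arms is affected.

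**What to change.** State one order for T0, T1 and T2: unstimulated saliva is collected, plaque is scored and crevicular cones are taken, all before probing depth and GI. Record visible blood in each saliva sample. Say what is done when the replacement cone is also bloody.

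At T0, choose cone sites by visible hyperplasia or edema, signs already named in section 2.2. Discard samples from sites or patients that probing then shows to be ineligible.

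**Cost.** Section 2.4 gives one examiner both the examinations and the collections, so no staff or procedures are added beyond noting blood. The downside is a few discarded T0 samples, because eligibility and pseudopocket status are confirmed only after sampling. At T1 and T2 the sites are already known, so the reordering itself loses no samples.

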### Anamnesis

2.8

Anamnesis will be performed in both groups. In addition to general patient health questions, demographic data (age, gender, marital status, occupation, educational level, living conditions, salary) and medical history data (primary complaint, current illness status, medical history, dental history, and medications) will be collected.

### Methodology used for the clinical evaluation of gingivitis

2.9

It will be performed by an evaluator calibrated with periodontal probe in millimeters (Periodontal probe from the University of North Carolina UNC-15 - Hu-Friedy^TM^). The periodontal probe will be inserted at all predetermined sites at the gingival margin of all teeth, 30 seconds will be waited and, at the smallest sign of bleeding, the presence or absence of bleeding will be noted, in a dichotomous manner, for that site.^[34]^ Gingival bleeding will be evaluated at 6 sites (mesiobuccal, buccal, distobuccal, mesiolingual, lingual, distolingual).

Gingival index:

Presence (1) of bleeding with probing at gingival margin,^[34]^ or

Absence (0) of bleeding with probing at gingival margin.^[34]^

The gingival Index will be presented in a percentage (%). The result will be based on the ratio of total sites to sites affected (with bleeding)^[34]^

Results will be considered indicative of gingivitis with ≥ 10% bleeding.^[13]^

### Experimental design

2.10

Immediately prior to periodontal treatment, the investigator will remove and open 1 envelope (without changing the numerical sequence of the other envelopes) and perform the indicated procedure. In this manner, the 34 patients will be allocated into the experimental or control groups, as follows:

**G1**- Control group (n = 17) - patients will receive scaling and oral hygiene guidance + application of placebo PDT.

**G2**- Experimental group (n = 17) - patients will be treated with scaling and oral hygiene guidance + PDT application. Photodynamic therapy will be performed at 8 sites with gingival hyperplasia (pseudopocket).

### Oral hygiene guidance (OHG)

2.11

Immediately prior to treatment all participants will receive OHG: BASS brushing technique, specifications for toothbrush (soft bristles, only two rows for hygiene below and above brackets, narrow, rectangular head), interdental brush (0.05 mm) and dental floss (with wax attached to the thread).

To ensure that participants are adhering to the guidelines, they will be asked to bring their brushes and floss to check if the brushing technique is being performed correctly.

At all meetings the participant will be questioned about the use of mouthwashes as it is prohibited during the study. If use is reported, the participant will be excluded from the study.

### Treatments

2.12

#### Periodontal treatment

2.12.1

Participants in both (G1 and G2) groups will receive periodontal treatment (scaling and root planing - SRP) with universal curettes (Hu-Friedy) and ultrasound (Ultrassom Dabi Atlante - Profi Neo US, Ribeirão Preto, Brazil) depending on their needs. The SRP will be done in one session. Periodontal treatment will be performed by only one experienced researcher, who will not do the periodontal exams. Periodontal reassessment will be performed after 7 and 21 days. All patients in the control group will receive SRP, but will receive only a simulation of photodynamic therapy. To remove supragingival dental biofilm the Gracey Curette #3-4 will be used for the free surfaces of the anterior teeth and #7-8 on the free surfaces of the posterior teeth.

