## Abstract

It is known that the presence of orthodontic brackets predisposes for a change in the biofilm, facilitating the development of gingivits. The sites are difficult to access with a toothbrush and periodontal curette, worsening inflammation, in addition, a gingival hyperplasia is associated with poor hygiene. The objective of this study is to evaluate the impact of photodinamyc therapy (PDT) as an adjuvant treatment, considering clinical immunoregulatory and microbiological parameters. This randomized, controlled, double-blind clinical study will include 34 patients, both genders, having used fixed appliance for more than 12 months, with gingivitis. Participants will be divided into two groups: G1 (n = 17)- Scaling and Root Planing + PDT placebo and G2 (n = 17)- Scaling and Root Planing + PDT. In G2 the following dosimetric parameters will be used: methylene blue 0.005%, λ= 660 nanometers (nm), 9 Joules (J) per site, irradiance= 3.5Watts (W)/ centimeters (cm), radiant exposure= 318J/cm^2^. All participants will receive oral hygiene guidance prior the curetes scaling. The clinical periodontal data to be analyzed are plaque index, gingival index and probing depth. Crevicular fluid, from 4 pre-determined sites and saliva, will be collected and analysed for IL-6, IL-1β, IL-8, TNF-α and IL-10 cytokines using ELISA (Enzyme immunoabsorption assay) method. Total *Bacteria* count will also be performed, by qPCR and *Universal16SrRNA* gene. All analysis will be realized using in the baseline (T_0_), 7 (T_1_) and 21 (T_2_) days after treatment. Oral health-related quality of life will be assessed using the OHIP-14 questionnaire at times T_0_ and T_2_. If sample distribution is normal, the Student T-test will be applied if it is not normal, the Mann-Whitney test will be used. The data will be presented in terms of ± PD and The significance level will be set at p < 0.05. Our results may improve quality of life and add data to establish a therapeutic alternative for gingivitis during the orthodontic treatment. Registration: clinicaltrials.gov NCT04037709. https://clinicaltrials.gov/ct2/show/NCT04037709 - Registered in July 2019.

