### Randomization

2.5

To randomly distribute the participants into the experimental groups, a 40-lot draw will be made using the Microsoft Excel program, version 2017. The distribution of groups will be identical (1: 1) for the two groups. The distribution will be done in a blocking fashion (8 groups of 5 patients). Opaque envelopes will be identified with sequential numbers (1 to 40) and there will be information about the corresponding experimental group in the order obtained in the draw. The envelopes will be sealed and will remain sealed in numerical order until the start of the periodontal treatments. The drawing and preparation of the envelopes will be performed by a person not involved in the study. Immediately prior to periodontal treatment the investigator responsible for treatment will open 1 envelope (without changing the numerical sequence) and perform the indicated procedure. Three additional patients will be included in each group in view of the dropout predicted in any clinical study (considering a dropout of 20%).

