For the treatment of gingivitis, the gold standard is usually scaling with a curette or ultrasound to remove biofilm.^[20]^ In this study, which considers the challenge of accessing difficult areas, such as in gingival hyperplasia, where the gum may cover the cervical base of the bracket and bands, photodynamic therapy was proposed as an adjuvant treatment, being appropriate for those areas where it is challenging for the curette to reach. The use of ultrasound was disregarded in this study, due to the possibility of bracket detachment with prolonged use, of ultrasound as shown by the Bonetti, 2014.^[10]^

The use of a photosensitizer associated with light at the appropriate wavelength was selected as the adjuvant therapy in this study because it is commonly understood that there is a need to decontaminate sites with gingivitis. PDT has been successfully used to treat periodontal diseases.^[22]^ The PDT ‘therapeutic window’ is effective in reducing the number of colonies or biofilm and may intensify the results of conventional mechanical treatments.^[25,31]^ In addition, while PDT is associated with coronary root scaling in this study, it has been shown to be effective as a primary therapy of choice in hard-to-reach areas, not just as adjunctive therapy.^[1]^

In Alvarenga's study, 2018^[35]^, a 50% attenuation of light at 3 mm from the laser probe was observed. The decrease in light, especially at deep sites where bacteria still remain viable, and the wide range of published results using fiber optics, convinced us to choose the trans-gingival method of application. In addition, a large amount of energy is lost as the fiber apparatus seal is still lacking.

Methylene blue is the most widely used PS in Brazil.^[27,28]^ It was chosen because it is already approved by ANVISA (the Brazilian Health Regulatory Agency), it is easily accessible in the market and it favors clinical applications, as the product is already designed for use in syringes.

Patients will be included according to Chapple, 2018,^[13]^ which characterizes gingivitis as when GI is greater than 10% and probing depth ≤ 3 mm from the distance of the Cemento-enamel Junction to the bottom of the pocket. Clinical signs of gingivitis inflammation will also be considered. Pseudo-pockets will be included in the study, and they will be preferred as choices as they are often areas difficult to access, where PDT can act very effectively.

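### The allocation envelope is opened before scaling, although only the later PDT or placebo step needs it; the instrument rule for scaling also needs one consistent statement

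*Protocol article*

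**What the plan says.** **Timing of the envelope.** Section 2.5 (Randomization): "Immediately prior to periodontal treatment the investigator responsible for treatment will open 1 envelope". Section 2.10 (Experimental design) repeats the rule: "Immediately prior to periodontal treatment, the investigator will remove and open 1 envelope".

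**Who knows the arm.** Section 2.6 (Study blinding): "Only the researcher responsible for conducting the treatments (who will open the randomized envelopes) will know which treatment is assigned to each patient". The patient, the data collector, the microbiologist and the statistician are blinded. The same section gives as a reason for patient blinding that "the periodontal treatment will be identical in both groups", and treats simulated PDT as a separate matter.

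**What the treatment is.** Section 2.12.1 defines periodontal treatment as scaling and root planing, given to both groups in one session by one experienced researcher who does no examinations. Section 2.12.2 places both PDT and placebo PDT after scaling.

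**Instruments.** Section 2.12.1 names universal curettes and "ultrasound (Ultrassom Dabi Atlante - Profi Neo US, Ribeirão Preto, Brazil) depending on their needs", and gives Gracey curette numbers for anterior and posterior teeth. The Discussion states: "The use of ultrasound was disregarded in this study, due to the possibility of bracket detachment with prolonged use". The Abstract mentions only curettes: "All participants will receive oral hygiene guidance prior the curetes scaling".

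**The concern.** Scaling is the active treatment shared by both arms, and the trial asks what PDT adds to it. The comparison is clean only if scaling is delivered alike in both arms. The operator has to know the arm to give PDT or its placebo, but not to scale. Opening the envelope first means that how thoroughly each patient is scaled is decided by someone who already knows whether PDT will follow. Blinded outcome assessment cannot repair this: if scaling differed by arm, a blinded examiner would correctly record its effect on the gingival index, and the analysis would attribute that effect to PDT.

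The instrument question is secondary. Taken at face value, the Methods and the Discussion leave a reader unsure whether PDT is added to curettes alone or to curettes plus ultrasound as needed.

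**Working it through.** The plan gives no figure to reproduce on this point. The check is of the order of steps, with a simple count.

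**1. Order of steps.**

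| Step | Section | Allocation needed? |
|---|---|---|
| Examination, questionnaire, sampling, hygiene guidance | 2.7, 2.11 | No |
| Envelope opened by the operator | 2.5, 2.10 | – |
| Scaling and root planing | 2.12.1 | No: meant to be identical (2.6) |
| PDT or placebo PDT | 2.12.2 | Yes |

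The envelope is opened one step before it is needed.

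**2. Could periodontal treatment mean the whole session, PDT included?** No. Section 2.6 calls the periodontal treatment identical in both groups and mentions PDT and its simulation separately. Section 2.12.1 equates the term with scaling and root planing.

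**3. How many patients.** 17 + 3 = 20 per arm (sections 2.1, 2.5 and 2.10), and 2 × 20 = 40. This matches the envelopes numbered 1 to 40 and the 8 blocks of 5 (8 × 5 = 40). The exposure applies to every treated patient.

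**4. Where the primary variable is sensitive.** The gingival index is the percentage of bleeding sites, six sites per tooth over all teeth (sections 2.9 and 2.14.3). PDT is applied at 8 sites (sections 2.10 and 2.12.2). The number of teeth is not given. If 24 to 28 are examined (an assumption), there are 6 × 24 = 144 to 6 × 28 = 168 sites. PDT then reaches 8/168 = 4.8% to 8/144 = 5.6% of them. Scaling is described for both anterior and posterior teeth, so it can act on more of the index than PDT does directly. This shows why equal scaling matters for this endpoint. It does not show that scaling will differ.

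**5. What moving the envelope achieves.** The operator would no longer know the current patient's arm while scaling. The same person has, however, opened every earlier envelope, and allocation is in blocks of 5, so later assignments might be partly guessed. The exposure falls but does not vanish.

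**6. Instruments side by side.** Section 2.12.1 permits ultrasound by need, with no limit on duration or place. The Discussion sets it aside for this study. Both are current text and they conflict on their face. The Discussion's reason refers to prolonged use, and the Introduction warns specifically against prolonged instrumentation at the bracket base, so a narrower meaning is possible. Section 2.12.1 does not say who judges need. It could be settled at the pretreatment examination, where "These data will be collected by 1 calibrated researcher".

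**The case against.** **The current order breaks no stated rule.** Envelopes are opaque, sealed, sequential, prepared by someone outside the study, and opened after baseline data are taken. Section 2.10 describes each arm as a package of scaling, guidance and PDT or placebo, so opening the envelope when the session starts is coherent, and many trials do so. This stands: there is no failure of allocation concealment, although a reader might infer one. The point concerns delivery of treatment after allocation.

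**Safeguards exist.** One experienced operator, one session, specified Gracey numbers, and an operator who does no examinations all limit variation. This stands in part: they limit differences between operators and protect measurement, but they do not fix one operator's effort from patient to patient.

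**An unblinded operator is unavoidable.** True for the PDT or placebo step, but not for scaling.

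**The ultrasound conflict is thin.** The Discussion may only reject prolonged ultrasound at the bracket base, and the Abstract's mention of curettes is shorthand about when hygiene guidance is given. Whichever reading is right, it applies to both arms. This largely stands. A reader might infer that the conflict itself biases the comparison, or that the operator picks the instrument freely while knowing the arm. The document supports neither: the conflict alone creates no difference between arms, and the text speaks of participants' needs without saying who assesses them.

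**Conclusion.** The point holds as an avoidable weakness in the order of procedures. Every patient, up to 40, is to be scaled by an operator who knows the arm without needing to. Scaling effort is therefore needlessly exposed to that knowledge, and the planned blinding cannot correct it. The statement in section 2.6 that scaling is identical is an intention that the procedure does not secure.

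No size or direction of bias is shown. A reader might infer that the result will favour PDT. The document supports no such claim, since it gives nothing on how scaling effort or ultrasound use would vary by arm or affect the gingival index.

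The conclusion rests on reading periodontal treatment as scaling and root planing, which the document itself does. It does not depend on the ultrasound question, which remains a wording inconsistency to be clarified.

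**What to change.** 1. Amend sections 2.5 and 2.10 so that the sealed, sequential envelope is opened after scaling is finished and immediately before the PDT or placebo step. The agent (methylene blue or its placebo vehicle) is then prepared after scaling.
2. State one instrument rule for both arms and make section 2.12.1, the Discussion and the Abstract agree with it. Either use curettes only, or allow ultrasound with the need recorded before the allocation is known, for example at the pretreatment examination in section 2.7. If the Discussion means only prolonged use at the bracket base, it should say so.

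The cost is a few changes of wording and a short preparation step between scaling and PDT. Concealment is kept, and no patient, visit or measurement is added. Some guessing from earlier allocations remains possible.
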